### Data collection

2.2

#### Instruments

2.2.1

The following screening instruments are being used for data collection:
The Center for Epidemiologic Studies Depression Scale (CES‐D)This scale was developed by the National Institute of Mental Health (NIMH) for epidemiological studies to detect depression in the general population.^25^ The CES‐D is a 20‐item self‐rating questionnaire that assesses symptoms of depression. The cut‐off value is 16 points, and a Japanese version of the CES‐D (CES‐D‐J) has been validated.^26^
The Edinburgh Postnatal Depression Scale (EPDS)The EPDS is a 10‐item self‐rating scale designed by British psychiatrist John Cox to screen for postpartum depression.^22^ The Japanese version of the EPDS was validated in 1996.^23^ Recently, the EPDS has also been shown to be a reliable and valid measure of maternal prenatal depression^27^ and is attracting attention as a rating scale for paternal perinatal depression.^8^ The diagnostic accuracy of the EPDS for postpartum depression in Japanese men has been reported to have a sensitivity of 81.8% and a specificity of 94.1% in the postpartum period, with a cutoff value of 8,^28^ but a similar study is lacking for the prenatal period.The Edinburgh Postnatal Depression Scale‐Partner (EPDS‐P)In regard to the original English‐language versions, the EPDS‐P was developed to assess postpartum depression in women from man’ perspective.^29^ In contrast, the EPDS‐P developed by Fisher et al.^24^ assesses paternal postpartum depression through maternal reporting. The diagnostic accuracy of the EPDS‐P has been reported to have a sensitivity of 89% and a specificity of 59% with a cutoff value of 4/5, but a Japanese version had yet to be developed. Therefore, with the help of [name], the English version of EPDS‐P for paternal depression was translated into Japanese, and back‐translated into English by three native speakers of Japanese and English and validated its Japanese version.The Mother‐to‐Infant Bonding Scale (MIBS)The MIBS is a self‐rating questionnaire that assesses a mother's feelings toward her infant.^30^ The MIBS includes 10 items that assess the mother–child bond.^31^ Each item is rated on a four‐point Likert‐type scale (0–3). The higher the MIBS score, the weaker the mother–child bond. The Japanese version of the MIBS has been previously validated and is commonly used in Japan to assess mother–child bonding.^31^

**FIGURE 1 npr212321-fig-0001:**
[figure not shown]
SPIRIT schedule. CES‐D, Center for Epidemiologic Studies Depression Scale; EPDS, Edinburgh Postnatal Depression Scale; EPDS‐P, Edinburgh Postnatal Depression Scale‐Partner.

**FIGURE 2 npr212321-fig-0002:**
[figure not shown]
Evaluation Direction of Rating Scales. CES‐D, Center for Epidemiologic Studies Depression Scale; EPDS, Edinburgh Postnatal Depression Scale; EPDS‐P, Edinburgh Postnatal Depression Scale‐Partner.

### Outcome measures

2.3

The primary outcome will be accuracy of the EPDS‐P in determining paternal perinatal depression in Japanese men. Presence of paternal depression is determined based on the CES‐D, with a CES‐D total score of 16 or higher considered depression.

Then, ROC curves are drawn and AUCs are calculated to examine the discrimination accuracy of the two groups (depression or not) by EPDS‐P. Discriminatory value of ROC curves was interpreted as excellent (AUC 0.9–1), good (0.8–0.89), fair (0.7–0.79), poor (0.6–0.69), or fail/no discriminatory capacity (0.5–0.59).^32^ On the other hand, the point on the ROC curve where “sensitivity + specificity” is maximized is defined as the optimal cut‐off point. The sensitivity and specificity at the cutoff point are calculated, respectively.

The secondary outcome will be whether prenatal EPDS‐P can predict paternal postpartum depression using longitudinal data from pregnancy and the early postpartum period. Furthermore, we will calculate the correlation between the EPDS and CES‐D in men and analyze the performance of the EPDS in identifying paternal perinatal depression.

### Sample size calculation

2.4

A meta‐analysis of reports based on self‐rating scales estimated the prevalence of paternal perinatal depression among Japanese men to be approximately 10%.^10^ Therefore, the sample size required to validate the accuracy of the EPDS‐P in the last trimester of pregnancy and within 3 months postpartum was estimated to be 554 at each time point, assuming a standard normal distribution, 95% confidence level, 0.025 margin of error (α/2), and 10% estimated value of the population proportion. Assuming a valid response rate of 90%, the target number of cases was set at 600 pairs for each time‐point. In Towada City, public health nurses have been making home visits to nearly all expectant and nursing mothers as part of the routine work of the maternal and child health care system since before this study began. An interview survey including the EPDS was conducted with women visited by these public health nurses, and cooperation was obtained in all cases. For this reason, we assumed that a high percentage of women would cooperate in the screening survey for paternal perinatal depression and therefore assumed the rate to be 90%. Given approximately 300 births per year and an extremely high rate (>95%) of home visits by public health nurses and midwives to expectant mothers in Towada City, the target number is expected to be achieved within a 30‐month survey period.

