### Strengths and limitations

2.9

This longitudinal observational study has a sufficient sample size compared with previous reports. A self‐rating scale is being used to assess the study participants, and the screening system using the self‐rating scales does not require technical proficiency to administer and answer, which makes it easy to apply in real‐world clinical practice. However, as a regional study, our findings might not be generalizable to other regions. In addition, assessment of perinatal depression using a self‐rating scale differs from psychiatric diagnosis based on a structured interview, and may not accurately reflect the mental status of the participants, and might include false positives and false negatives of depression.

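### The 554 in Section 2.4 is the sample size for estimating a 10% prevalence to ±2.5 points, so it does not justify the primary outcome, EPDS-P accuracy

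*Protocol article*

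**What the plan says.** Section 2.3 (Outcome measures) sets the target: "The primary outcome will be accuracy of the EPDS‐P in determining paternal perinatal depression in Japanese men". Accuracy there means the AUC of the EPDS-P against a CES-D score of 16 or more, with sensitivity and specificity at the cut-off that maximises their sum. Sections 2.3 and 2.5 also attach a verbal grade to the AUC, in bands about 0.10 wide.

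Section 2.4 (Sample size calculation) begins from a meta-analysis that "estimated the prevalence of paternal perinatal depression among Japanese men to be approximately 10" per cent. From this it derives its figure, "554 at each time point", and gives its purpose in these words: "the sample size required to validate the accuracy of the EPDS‐P in the last trimester of pregnancy and within 3 months postpartum was estimated". The inputs listed are a "95% confidence level, 0.025 margin of error (α/2), and 10% estimated value of the population proportion". It continues: "Assuming a valid response rate of 90%, the target number of cases was set at 600 pairs for each time‐point".

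Section 2.9 (Strengths and limitations) adds: "This longitudinal observational study has a sufficient sample size compared with previous reports".

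**The concern.** The calculation begins with how common paternal depression is and ends with a statement about how well the EPDS-P detects it. These are different estimands with different denominators. Prevalence uses every man. Sensitivity uses only men with CES-D 16 or more, about one in ten on the protocol's assumption. Specificity uses only the others. A sample size for the first says nothing directly about the other two, or about the AUC.

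The margin is also tagged as α/2. A margin of error is a half-width on the scale of the proportion, whereas α/2 is a tail probability. Both equal 0.025 here, but they are not the same thing.

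At stake is the stated basis of the primary outcome. As written, Section 2.4 tells the reader that the study was sized for accuracy, and its own inputs show otherwise. It also does not tell the reader that sensitivity will rest on roughly 54 or 55 men.

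**Working it through.** **1. Reproduce the protocol's figure.** Inputs from Section 2.4: p = 0.10, d = 0.025, z = 1.96.

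n = z² p(1 − p) / d² = 1.96² × 0.10 × 0.90 / 0.025² = 553.2, rounded up to 554. This matches exactly, so there is no arithmetic slip. The p in the formula is the prevalence of paternal depression.

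**2. Expected numbers.** 600 × 0.9 = 540 valid pairs. (554 / 0.9 is 616, so 540 is slightly below 554; the gap is small and not part of this point.) At 10% prevalence, 540 pairs give 54 cases and 486 non-cases.

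**3. Sensitivity and specificity.** Half-width = 1.96 × √(p(1 − p)/m), with m the relevant denominator. The only EPDS-P accuracy values in the document are those of the cited US study (Introduction and Section 2.2.1): sensitivity 0.89, specificity 0.59. The other values are assumptions.

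| Quantity | Calculation | 95% half-width |
|---|---|---|
| Sensitivity 0.89 (cited) | 1.96 × √(0.89 × 0.11 / 54) | ±8.3 points |
| Sensitivity 0.80 (assumed) | 1.96 × √(0.80 × 0.20 / 54) | ±10.7 points |
| Sensitivity 0.70 (assumed) | 1.96 × √(0.70 × 0.30 / 54) | ±12.2 points |
| Specificity 0.59 (cited) | 1.96 × √(0.59 × 0.41 / 486) | ±4.4 points |

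Near 0.89 the interval is not symmetric: the Wilson interval is about 78% to 95%.

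**4. AUC.** Hanley–McNeil variance, with n₁ = 54 and n₀ = 486:

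[A(1 − A) + (n₁ − 1)(Q₁ − A²) + (n₀ − 1)(Q₂ − A²)] / (n₁n₀), where Q₁ = A/(2 − A) and Q₂ = 2A²/(1 + A).

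| Assumed AUC | SE | 95% half-width |
|---|---|---|
| 0.70 | 0.0413 | ±0.081 |
| 0.80 | 0.0371 | ±0.073 |
| 0.90 | 0.0284 | ±0.056 |

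The full interval is therefore about 0.11 to 0.16 wide, wider than one of the grading bands.

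**5. Dependence on prevalence.** At N = 554 and sensitivity 0.89, a prevalence of 8.4% (the international figure in the Introduction) gives 46.5 cases and ±9.0 points. An assumed 20% gives 110.8 cases and ±5.8 points. The mismatch does not depend on the 10% assumption.

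**6. What is left out.** Steps 3 and 4 cover sampling error only, and step 3 treats the cut-off as fixed. Section 2.5 chooses the cut-off on the same data, which adds optimism to the reported sensitivity and specificity that is not counted here.

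**The case against.** The strongest reply is that the protocol never promises a precision for accuracy. Section 2.4 gives its inputs openly, as a "0.025 margin of error (α/2), and 10% estimated value of the population proportion", and no section states a half-width for sensitivity, specificity or AUC. That stands. A reader might infer that EPDS-P accuracy will be known to ±2.5 points, because that margin sits beside a sample size said to serve accuracy. The document does not say so. It would therefore be unfair to work out how many couples ±2.5 points on sensitivity would need and call the difference a shortfall: nobody set that target. Nor do the documents show that about 54 cases is too few; 600 pairs remains informative.

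A reader might also take the strength claimed in Section 2.9 to be false. It is a comparison with earlier studies, which the Abstract describes as relatively small. Those studies are not in the documents, so the sentence cannot be refuted from them.

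The AUC bands are conventional descriptive grades with no decision attached, so their use is not an error. Grading by the lower confidence limit would be a poor remedy. At a true AUC of 0.85 (SE 0.0335, half-width 0.066), the lower limit falls below 0.80 whenever the estimate is below 0.866. The probability is about Φ((0.866 − 0.85)/0.0335) = Φ(0.47) ≈ 0.68, so a truly good AUC would usually be under-graded.

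What the reply does not rescue is the sentence in Section 2.4. The calculation is given in full there and is attributed to accuracy, so this is not a detail left to a fuller document.

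**Conclusion.** The point holds as a mismatch between the justification and the primary outcome. The number 554 is computed correctly but answers a prevalence question, and Section 2.4 is wrong to present it as the size needed for accuracy. The α/2 tag is a labelling error that changes no number.

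The size of the matter is the difference between what the calculation delivers (±2.5 points on prevalence) and what the same sample gives on accuracy: roughly ±8 to ±12 points on sensitivity between 0.89 and 0.70, about ±4 points on specificity near 0.59, and about ±0.06 to ±0.08 on AUC. These figures assume 540 valid pairs, 10% prevalence and a fixed cut-off. The true accuracy in this population is unknown, which is why a range is needed and not the single figure at 0.89. The conclusion does not extend to a claim that the study is too small or that it broke a stated precision target.

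**What to change.** Keep 600 pairs and rewrite Section 2.4 as follows.

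- Say that 554 gives ±2.5 points on a prevalence of 10%, and nothing more. Remove the wording that makes it the size needed for validating accuracy, and remove the α/2 tag from the margin.
- State the expected case and non-case counts (54 and 486 from 540 valid pairs at 10% prevalence).
- Give the expected accuracy precision as a range with its assumptions: ±8.3, ±10.7 and ±12.2 points at sensitivity 0.89, 0.80 and 0.70; ±4.4 points at specificity 0.59; ±0.081 to ±0.056 for AUC 0.70 to 0.90.
- Note that the sensitivity and specificity figures treat the cut-off as fixed, and that choosing it on the same data makes the reported values optimistic.

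In Sections 2.3 and 2.5, report the AUC grade together with its 95% interval, and leave the grade on the point estimate. Section 2.9 need not change on this account.

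The cost is wording only. No further couples, data or analyses of a new kind are needed beyond the interval, and the stated precision becomes less favourable.

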## INTRODUCTION

1

Perinatal depression is a psychiatric disorder that occurs during pregnancy and within the first year postpartum, and it is known to increase the risk of adverse impacts on child development.^1^, ^2^, ^3^, ^4^ Known causes of maternal perinatal depression include biological, psychological, and social problems, with family support having a strong positive impact on women's mental health.^5^ For this reason, men are generally encouraged to assist women and children during the perinatal period.^6^ It has become clear that men may also experience psychosocial crises and high rates of depression during the perinatal period.^7^ An international meta‐analysis found the prevalence of paternal perinatal depression to be 8.4%.^8^ In addition, paternal perinatal depression is known to increase the risk of suicide in men.^9^ Our previous meta‐analysis found the prevalence of perinatal depression among Japanese men to be approximately 10%, with no statistically significant difference in prevalence between men and women in terms of relative risk.^10^ Risks of maternal and paternal perinatal depression as well as child abuse are reported to correlate with each other.^9^, ^11^ This suggests that supporting the father might ultimately have a positive impact on the mental stability of the mother and on the development of the child.^12^ Therefore, it is necessary to assess the mental state of men as well as of women, and to provide appropriate support during the perinatal period. However, men are less likely to participate in the perinatal support system than are women.

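### At the stated 90% valid response rate, 600 pairs yield 540 valid pairs rather than the required 554, and the 90% is justified from women only

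*Protocol article*

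**What the plan says.** Section 2.4 (Sample size calculation) of the Protocol article sizes the study by the precision of a single proportion. The inputs are a "10% estimated value of the population proportion", a 95% confidence level and a margin of error of 0.025. The required number "was estimated to be 554 at each time point". The next sentence allows for unusable responses: "Assuming a valid response rate of 90%, the target number of cases was set at 600 pairs for each time‐point".

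The section then justifies the 90%. Public health nurses had already surveyed the women they visited, with the EPDS included, and every woman cooperated. From this the authors write that "we assumed that a high percentage of women would cooperate in the screening survey for paternal perinatal depression", and they set the rate at 90%. No rate is given for men or for couples.

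Other sections define what a usable pair is. Under Instruments (2.2.1), women complete the EPDS-P and men complete the CES-D. Under Outcome measures (2.3) and Data analysis plan (2.5), the man's CES-D total of 16 or more defines depression, and the EPDS-P is judged against it. The Data analysis plan also leaves out responses with missing values or an inappropriate number of answers on a scale. The Introduction remarks that "men are less likely to participate in the perinatal support system than are women".

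**The concern.** There are two problems, one arithmetical and one about the basis of the rate.

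First, a requirement of 554 valid pairs and a valid rate of 90% imply a target above 600. The stated target therefore misses the stated requirement on the section's own figures.

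Second, the 90% is applied to pairs, but its only support is that women cooperated with an interview about themselves. A pair enters the primary analysis only if the woman's EPDS-P and the man's CES-D are both complete. The rationale covers one half of the pair and is silent on the half that supplies the reference standard.

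What is at stake is the precision the study can claim. The number of depressed men is about a tenth of the valid pairs, and it governs how well sensitivity is estimated.

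**Working it through.** **Inputs.** From section 2.4: p = 0.10, half-width d = 0.025, 95% confidence (z = 1.96), required n = 554, valid rate 0.90, target 600 pairs. From the Introduction: 89% sensitivity reported for the EPDS-P in the United States, used here only to illustrate precision.

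**Step 1: the plan's own figure.** n = z² p(1 − p)/d² = 1.96² × 0.09/0.025² = 553.2, rounded up to 554. The figure reproduces exactly.

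**Step 2: allowance for invalid responses.**
- Dividing by the valid rate: 554/0.90 = 615.6, so 616 pairs.
- The common shortcut of adding 10%: 554 × 1.10 = 609.4, so 610 pairs.
- Neither gives 600.

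**Step 3: what 600 pairs deliver.**
- Valid pairs at 90%: 600 × 0.90 = 540, and 554 − 540 = 14 short.
- Valid rate at which 600 is enough: 554/600 = 92.3%.
- Half-width at 540: 1.96 × √(0.09/540) = 0.0253, against 0.0250 planned.
- Depressed men expected at 10%: 54, against about 55 for 554 pairs.
- 95% half-width for a sensitivity of 89%: 1.96 × √(0.89 × 0.11/55) = 8.3 points with 55 men, and 8.3 points (8.35 against 8.27) with 54.

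**Step 4: sensitivity to the pair-level rate.** The documents give no rate for men, so the rates below are assumptions. The 81% is what 90% for each partner would give if the two were independent (0.90 × 0.90). The 90% row is the plan's own assumption.

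| Pair-level valid rate | Valid pairs from 600 | Half-width at 10% (points) | Depressed men expected | Half-width, sensitivity 89% (points) | Pairs needed for 554 valid |
|---|---|---|---|---|---|
| 90% | 540 | 2.53 | 54 | 8.3 | 616 |
| 81% | 486 | 2.67 | 49 | 8.8 | 684 |
| 70% | 420 | 2.87 | 42 | 9.5 | 792 |
| 60% | 360 | 3.10 | 36 | 10.2 | 924 |

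The half-widths in the third column are 1.96 × √(0.09/n), those in the fifth 1.96 × √(0.89 × 0.11/m), with n valid pairs and m depressed men.

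**The case against.** The strongest reply is that the arithmetic gap is of rounding size. Fourteen pairs out of 554 is 2.5%, the half-width moves by 0.03 of a point, and one fewer depressed man is expected. No analysis or conclusion would change. This stands, and it sets the weight of the point. It does not remove the inconsistency, because a minimum requirement is not met by rounding the target down.

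A second reply is that the 600 are pairs, and written consent is obtained from all participants. On the natural reading, a father has already agreed when his pair counts towards 600, so his willingness to consent affects accrual and not validity within pairs. This largely stands. What remains is whether consenting men return a complete CES-D, and a rate drawn from women does not speak to that.

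A reader might infer several stronger things that the documents do not support:
- *That the number of depressed men must fall well below 55.* No paternal response rate is given. The Introduction's remark concerns men's use of perinatal support services, gives no figure, and does not address questionnaire completion.
- *That the 30-month feasibility statement rests on the wrong rate.* That sentence uses about 300 births a year and home visits above 95%, not the 90%. Its inputs give at least 300 × 2.5 × 0.95 = 712 visited mothers, more than 600 or 616.
- *That the calculation wrongly ignores loss between pregnancy and postpartum.* Section 2.4 sizes each time point separately, and the primary accuracy analysis is done at each. The longitudinal question is a secondary outcome that the section does not claim to size.

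**Conclusion.** The point holds as a minor one. On section 2.4's own inputs, 600 pairs yield 540 valid pairs where 554 are required; 616 would be needed. This part rests on no outside assumption, and its effect is small: ±2.53 instead of ±2.50 points, and about 54 instead of 55 depressed men.

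The stated reason for the 90% also does not support its use for pairs, because it covers women's cooperation only while the reference standard comes from the man. That follows from the text. How much it matters cannot be read from the documents: the 81%, 70% and 60% rows show what would follow if those rates applied, not what should be expected.

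**What to change.** In section 2.4, do one of two things: state a target of 616 pairs per time point, or keep 600 and state that at 90% it yields 540 valid pairs with a half-width of 2.53 points.

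In either case, replace the women-only justification with a couple-level rate, defined as the proportion of enrolled pairs with both the woman's EPDS-P and the man's CES-D complete at the time point. Recruitment has run since October 2021, so an observed rate can be tabulated. Then restate the expected number of valid pairs, the expected number of depressed men and the resulting precision.

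The cost is a few sentences and one tabulation. Restating what 600 delivers obliges no one to enrol more couples, though the stated figures become slightly less favourable.

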### Data analysis plan

2.5

Upon completion of data collection, the database will be locked for statistical analysis. First, we will calculate the screening accuracy of the EPDS‐P, which in this study assesses depressive symptoms in men by women.

Men with a CES‐D score of 16 or higher are defined as the “depressed” group, and those with a CES‐D score of 15 or lower are defined as the “non‐depressed” group. ROC curves are drawn and AUCs are calculated to examine the discrimination accuracy of the two groups by EPDS‐P score. The discriminatory value of the ROC curves is interpreted as follows: excellent (AUC 0.90–1.00), good (0.80–0.89), fair (0.70–0.79), poor (0.60–0.69), or fail/no discriminatory capacity (0.5–0.59).^32^ The point on the ROC curve where sensitivity + specificity is maximized is defined as the optimal cut‐off point, and the sensitivity and specificity at the cut‐off point are calculated separately.

Next, we will determine the absolute value of Spearman's non‐parametric correlation coefficient between the EPDS‐P and CES‐D. We will also set men scoring 16 or higher on the CES‐D as the depressed group,^26^ and then perform a receiver operating characteristic (ROC) curves analysis to calculate optimal cut‐off values and sensitivity and specificity of the EPDS‐P. We also plan to examine the reliability of the EPDS‐P by calculating its Cronbach's alpha. Cronbach's alpha is the most widely used objective measure of reliability. Alpha is an important concept in the evaluation of assessments and questionnaires. Cronbach's alpha is a confidence coefficient that evaluates whether or not the items measure the same concept or object as a whole (internal consistency) when multiple questions are asked about a characteristic, and the sum of the responses is used as the characteristic scale.^33^ If the Cronbach's alpha coefficient for each item is above 0.6, it is considered to have good internal stability, reliability, and acceptable consistency for an exploratory study.^34^

The cut‐off value of the EPDS‐P in detecting paternal depression will be calculated at two points: in late pregnancy and within 3 months postpartum. The statistical analysis did not include any participant's response having missing values or an inappropriate number of answers to a question item on a rating scale. Then, as a secondary analysis, we would like to stratify depressed and non‐depressed women, analyze the accuracy of the EPDS‐P in identifying paternal perinatal depression in each group, and examine the impact of women's mental status on the accuracy of the EPDS‐P.

In addition, we will examine the absolute value of Spearman's non‐parametric correlation coefficient between the CES‐D and EPDS in men and the accuracy of the EPDS in identifying depression in men. The depression group is defined as those with a CES‐D score of 16 or higher. Based on this, participants are divided into a depression group or a non‐depression group. We will also report the sensitivity and specificity of the cut‐off points for the EPDS in men at the pregnancy and postpartum. The global performance of the EPDS in men will be expressed as area under the ROC curve.

We will also analyze the characteristics of participants who first developed depression after childbirth.

As with maternal depression, paternal postpartum depression might develop during pregnancy, so we will calculate the proportion of cases of paternal postpartum depression that develop throughout the prenatal to postpartum period.

We will examine whether EPDS‐P scores during pregnancy predict paternal postpartum depression. First, postpartum men will be divided into two groups: a depressed group (CES‐D total score of 16 or higher) and a non‐depressed group (CES‐D total score of 15 or lower). We will then draw an ROC curve using the EPDS‐P score during pregnancy and calculate the area under the ROC curve (AUC). The discriminatory value of the ROC curves will be interpreted as follows: excellent (AUC 0.90–1.00), good (0.80–0.89), fair (0.70–0.79), poor (0.60–0.69), or fail/no discriminatory capacity (0.50–0.59).^32^ If the AUC value is large, it is considered that the EPDS‐P score during pregnancy can discriminate paternal postpartum depression because EPDS‐P score during pregnancy can predict paternal postpartum depression. We will then determine the EPDS‐P optimal cutoff value during pregnancy that most accurately identifies paternal postpartum depression (the point on the ROC curve where sensitivity + specificity is maximized).

Furthermore, we will use a covariance structure analysis and binomial logistic regression analysis to test whether maternal EPDS score, MIBS score, and other maternal characteristics affect their EPDS‐P scores. All statistical analyses will be performed using IBM SPSS 28 and Amos 28 (IBM Japan, Tokyo, Japan).

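### EPDS-P sensitivity and specificity are reported from the same data that chose the cut-off, so the pair (not the AUC) is modestly biased in the tool's favour

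*Protocol article*

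**What the plan says.** Section 2.3 (Outcome measures) sets the endpoint: "The primary outcome will be accuracy of the EPDS‐P in determining paternal perinatal depression in Japanese men". Depression is defined as a CES-D total of 16 or more. The AUC is graded against fixed bands, and the cut-off is the point where the sum of sensitivity and specificity is largest. The section continues: "The sensitivity and specificity at the cutoff point are calculated, respectively".

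Section 2.5 (Data analysis plan) repeats the rule, "The point on the ROC curve where sensitivity + specificity is maximized is defined as the optimal cut‐off point", and adds that "the sensitivity and specificity at the cut‐off point are calculated separately". It applies the rule twice: "The cut‐off value of the EPDS‐P in detecting paternal depression will be calculated at two points: in late pregnancy and within 3 months postpartum". The same maximisation is used to find a pregnancy EPDS-P cut-off for postpartum depression.

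Section 2.2.1 (Instruments) cites an EPDS-P threshold from earlier work, "sensitivity of 89% and a specificity of 59% with a cutoff value of 4/5", and a male EPDS cut-off of 8 for the postpartum period. Neither is named in section 2.5 as a threshold to be evaluated. The limitations in section 2.9 discuss self-rating and regional scope, but not the selection of the cut-off.

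**The concern.** A threshold picked because it gave the largest sum in this sample will, on average, owe part of that sum to chance. The sensitivity and specificity read off at that point are then better than the tool would achieve at the same threshold in new couples. An ordinary confidence interval at the selected cut-off does not show this, because it treats the cut-off as fixed in advance.

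The exposure depends on the number of depressed men, not the number of couples. The sample size in section 2.4 rests on the precision of a prevalence, so it gives no assurance about sensitivity or about the stability of the cut-off. Section 2.8.2 expects the work to establish a screening system. The threshold and its sensitivity and specificity are therefore the figures most likely to be carried into practice.

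**Working it through.** **1. The plan's own figure.** Section 2.4 uses a 95% level, a margin of 0.025 and a proportion of 10%:

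n = 1.96² × 0.10 × 0.90 / 0.025² = 553.2, rounded up to 554. This reproduces the stated figure, and it is the precision of a prevalence.

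**2. Expected depressed men.** The article cites a meta-analysis that "estimated the prevalence of paternal perinatal depression among Japanese men to be approximately 10" per cent. With 600 pairs and a 90% valid response: 600 × 0.90 = 540 valid pairs, and 540 × 0.10 = 54 depressed and 486 non-depressed men per time point.

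**3. Sampling error at a fixed cut-off**, for scale. Half-width = 1.96 × √(Se(1 − Se)/54):
- Se 0.65: ±12.7 points
- Se 0.70: ±12.2 points
- Se 0.80: ±10.7 points

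**4. Selection bias by simulation.** The article gives no EPDS-P score distribution, so one has to be assumed: integer scores 0 to 30 from truncated negative binomials. In each replicate the cut-off with the largest sum was chosen. The apparent values were compared with the true values at that same cut-off. J is sensitivity + specificity − 1.

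Setting A: 54 and 486 men, mean 3.5 in the non-depressed, dispersion 2.5 (depressed) and 1.2 (non-depressed), 20,000 replicates.

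| True AUC | Apparent J | Excess in J | Excess in sensitivity | Excess in specificity | Cut-off, 5th–95th percentile |
|---|---|---|---|---|---|
| 0.665 | 0.276 | 0.042 | 0.037 | 0.004 | 2–6 |
| 0.711 | 0.341 | 0.041 | 0.037 | 0.004 | 3–6 |
| 0.765 | 0.420 | 0.038 | 0.034 | 0.004 | 3–7 |
| 0.816 | 0.502 | 0.036 | 0.032 | 0.003 | 4–8 |

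At AUC 0.765 the best J attainable is 0.395. The plan would report 0.420 on average, while the chosen cut-offs achieve 0.420 − 0.038 = 0.382. Across the four rows the chosen cut-off equals the true optimum in 31% to 34% of samples and lies within one point of it in 75% to 81%.

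Setting B: mean 4 in the non-depressed, dispersion 1.5, 4,000 replicates. At AUC 0.78, apparent J is 0.459 against a true 0.420, sensitivity is 0.651 against 0.616 (3.5 points), and the cut-off range is 5 to 10. At AUC 0.69, J is 0.311 against 0.265 and the cut-off range is 4 to 10.

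Further runs with other dispersions stayed close to these: about 3 to 4.6 points in sensitivity, 0.3 to 0.5 in specificity, and a cut-off span of 3 to 7 score points.

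**5. Control.** At a cut-off fixed beforehand (5 or more, that is 4/5), the same simulations show no average bias. The excess therefore comes from the selection step.

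**6. Relative size.** At a sensitivity of about 0.65, 3.5 / 12.7 = 0.28. The bias is roughly a third of the random error or a little less.

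**The case against.** The strongest case against is one of scope and size, and most of it stands.

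- **AUC.** A reader might infer that the whole primary accuracy result is inflated. It is not. The AUC, the only measure graded against bands, does not depend on a cut-off.
- **Every ROC analysis.** A reader might extend the point to all of them. For prenatal prediction, section 2.5 states an AUC and a cut-off, but not that sensitivity and specificity will be reported. For the male EPDS it promises both at the cut-off points without naming a maximisation rule, so the cited cut-off of 8 may be among those evaluated. For depressed and non-depressed women it promises accuracy in each group, but does not say that cut-offs are searched again there.
- **Larger bias in strata.** Bias does grow as cases fall: illustrative groups of 15 or 25 depressed men gave about 7 to 11 points in the sum. That needs a new search within strata whose sizes the article does not give, so it remains hypothetical.
- **Different thresholds by time.** The plan calculates a cut-off at each time point. It does not plan to test or claim a difference.
- **Missing detail.** Bootstrap methods and intervals may be left to an analysis plan that is not shown, so their absence is not the fault here. What remains is a rule that the article states: select and evaluate on the same data.
- **Usual practice, small bias.** Maximising the sum is common when a first cut-off is derived for a new language version, and the bias is well below sampling error. This limits the severity. It does not remove a bias whose direction is known and which can be corrected from the same data.
- **The cited 4/5 comes from the United States.** The article itself notes that EPDS cut-offs vary between countries. Accuracy at 4/5 is therefore an unselected estimate at one threshold, not evidence that it suits Japan.

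**Conclusion.** The point holds for EPDS-P sensitivity and specificity at the two time points. With about 54 depressed men, sensitivity would be overstated by about 3 to 4.5 percentage points on average and specificity by no more than about 0.5. The selected cut-off would vary over about 3 to 7 score points between the 5th and 95th percentiles. The sizes rest on 540 valid pairs, 10% prevalence and assumed negative binomial scores with a true AUC of roughly 0.65 to 0.82. The cut-off range is the figure most sensitive to the assumed distribution. The upward direction does not depend on it.

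The instability of the cut-off matters more in practice than the average bias. Neither undermines the AUC, the data collection or the sample. This should be fixed, but it does not threaten the study.

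**What to change.** Amend section 2.5 before the database is locked:

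1. Repeat the full EPDS-P cut-off search within at least 1,000 bootstrap samples. Report optimism-corrected sensitivity and specificity with 95% intervals, and the bootstrap interval of the cut-off itself. Do the same wherever else a cut-off is derived: the prenatal prediction analysis, and the male EPDS or the maternal strata if cut-offs are searched there.
2. Also report sensitivity and specificity with 95% confidence intervals at thresholds fixed before these data: EPDS-P 4/5 at both time points, and male EPDS 8 postpartum only, the period for which it is cited. Label these as unselected estimates.
3. If the pregnancy and postpartum cut-offs are compared, use a paired bootstrap of their difference that resamples couples, because the study follows the same couples over time.

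The cost is a short script, a few table rows and slightly lower reported accuracy. No extra data are needed.
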